#### **7.1.3. Justification of the efficacy endpoints**

The primary efficacy endpoint in this study is the proportion of patients who achieved a PASI 75 response at Week 16. This is a sensitive endpoint to assess the efficacy of BCD-057/Humira® in patients with moderate-to-severe plaque psoriasis. This measure is widely used in clinical studies of medicinal products for the treatment of psoriasis and is recommended by the EMA's *Guideline on Clinical Investigation of Medicinal Products Indicated for the Treatment of Psoriasis* (EMA/CHMP/EWP/2454/02). The time of the primary endpoint evaluation was chosen based on the PK of adalimumab (time to steady state) and is appropriate to evaluate the drug effects according to the EMA's guideline. The use of PASI alone may be not enough for the comprehensive efficacy assessment, so the clinical course of psoriasis in the study will be assessed in detail by analyzing the changes in the BSA, changes in the sPGA score, changes in the absolute PASI scores, and other indicators. This agrees with the EMA's *Guideline on Clinical Investigation of Medicinal Products Indicated for the Treatment of Psoriasis* (EMA/CHMP/EWP/2454/02).

The follow-up of patients does not stop after the data necessary for the primary endpoint analysis are obtained. The above said variables are assessed throughout the entire study (for about 1 calendar year). The duration of this study allows for assessing the long-term efficacy measures. It agrees with the recommendations provided in the EMA's *Guideline on Clinical Investigation of Medicinal Products Indicated for the Treatment of Psoriasis* (EMA/CHMP/EWP/2454/02).

## ***7.2. Methods and timeframes for assessment, documenting, and analysis of efficacy variables***

### ***7.2.1 Timeframes for analysis of efficacy variables***

The analysis of the primary efficacy endpoint will be performed at Week 16 of the blinded therapy with BCD-057/Humira®.

The secondary endpoints (at weeks 24, 33, and 55) will be analyzed when these results are obtained.

### ***7.2.2 Methods and timeframes for assessment and documenting of efficacy variables***

To assess whether the study has achieved its objective and to evaluate the treatment efficacy, the analysis will be performed in two populations: the ITT (intent-to-treat) population (all randomized patients) and the PP (per protocol) population (includes subjects who have no major protocol deviations up to and including Week 16).

The treatment efficacy will be assessed with the PASI, sPGA, BSA, and the health-related QoL scores (DLQI and SF-36).

## 8. Safety evaluation

### 8.1. List of safety variables

#### 8.1.1. Terms and Definitions

##### 8.1.1.1. Adverse events

An Adverse Event (AE) is any untoward medical occurrence in a patient or clinical investigation subject administered a pharmaceutical product and which does not necessarily have to have a causal relationship with this treatment.

An adverse event (AE) can therefore be any unfavorable and unintended sign (including an abnormal laboratory finding), symptom, or disease temporally associated with the use of a medicinal product, whether or not related to the medicinal product: from treatment initiation through 28 days after patient's withdrawal from the clinical study.

##### 8.1.1.2. Serious adverse events

A Serious Adverse Event (SAE) is any untoward medical occurrence that at any dose:

- Results in death
- Is life-threatening
- Requires hospitalization or its prolongation
- Results in persistent or significant incapacitation or disability
- Is a congenital anomaly or birth defect.

In case of any uncertainty whether the event meets the seriousness criteria or not, it should be treated as as a serious adverse event.

An immediate risk of death from a reported event is considered life-threatening. A life-threatening event does not include an adverse event that, had it occurred in a more severe form, might have caused death, but is not associated with an immediate risk of death in the form it occurred. For example, hepatitis resolved without signs of hepatic insufficiency will not be considered life-threatening in spite of the fact that more severe hepatitis can lead to fatal outcome. Similarly, an allergic reaction resulting in face angioedema will not be considered life-threatening, although larynx angioedema, allergic bronchospasm or anaphylaxis can lead to fatal outcome.

**Hospitalization** is an official admission to the hospital. Hospitalization or its prolongation is a criteria of AE seriousness; however, hospitalization itself is not a serious adverse event. Hospitalization or its prolongation not associated with an AE should not be reported by the investigator as a serious adverse event. This is applicable (including but not limited) to the following cases:

- Hospitalization or prolongation of existing hospitalization is necessary to perform procedures required by the Protocol.
- Hospitalization or prolongation of existing hospitalization is a part of routine procedures in this study site (for example, stent removal after a surgery). An appropriate confirmation should be kept in a study file.
- Hospitalization due to a pre-existing condition which did not aggravate.

**Disability** is a significant impairment of the patient's ability to live normal life.

**Other reportable information.** Certain information not considered an SAE must be recorded, presented in the report, and followed up as an SAE. This includes:

The use of the investigational product during pregnancy. If the pregnancy is confirmed, the study therapy should be discontinued immediately.

- The use of the investigational product during breastfeeding, regardless of AE development.
- An overdose with the study drug as defined in the Protocol, whether or not it was associated with an AE.
- Unintentional or accidental use of the investigational product, whether or not considered related to an AE.
- Medication errors whether or not considered related to an AE (including confusion or possible confusion during the administration of investigational products).
- Death whether or not associated with an AE.

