##### ***1.4.2. Risk assessment***

Considering the wide clinical experience gained with the originator Humira® and results from previous clinical studies, it can be concluded that the safety of adalimumab has been well investigated.

The most dangerous adverse effects of adalimumab include serious infections and malignancies [6].

Serious infections that have been reported with adalimumab include tuberculosis, bacterial sepsis, invasive fungal diseases (such as histoplasmosis), and opportunistic infections caused by opportunistic bacteria, viruses, mycobacterium, fungi, parasites, or other microorganisms. In 34 controlled clinical studies, the risk of serious infections in patients receiving adalimumab was 4.6

cases per 100 patient-years, while that for placebo was 3.1 cases per 100 patient-years. In 47 controlled clinical studies, the incidence of tuberculosis was 0.22 cases per 100 patient-years and the risk of tuberculin test conversion was 0.08 per 100 patient-years. Most cases of tuberculosis were recorded during the first 8 months of therapy with adalimumab. This may suggest reactivation of the latent infection. Some cases of tuberculosis resulted in death. In three pivotal studies where patients received adalimumab for psoriasis, no cases of tuberculosis were reported. The M04-716 study involved 89 patients with psoriasis and latent tuberculosis. All patients received preventive treatment for 9 months, and only 2 patients (2.2%) developed the active disease during the treatment with adalimumab.

Malignancies have been reported in patients receiving adalimumab. In controlled clinical trials, the incidence of malignancies in psoriasis patients receiving adalimumab was 2.4 cases per 100 patient-years vs. 1.4 cases per 100 patient-years with placebo [7].

In controlled clinical studies, psoriasis patients receiving Humira® developed the following adverse events.

Infections (nasopharyngitis, upper respiratory tract infections, and sinusitis) were the most common AEs. In clinical studies in psoriasis, subjects receiving adalimumab developed infections more frequently than subjects receiving placebo (30.3% vs. 23.9%) [7].

Injection site reactions (erythema, itch, pain, and swelling in the injection site) were also more frequent in patients receiving adalimumab than in patients receiving placebo (7.0% vs. 5.0%) [7].

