### ***6.1.3. Adjustment and discontinuation of study therapy***

#### ***6.1.3.1. Dose modification and discontinuation for the test or reference drug***

No dose modifications are allowed either for BCD-057 or Humira®. The patients should not compensate for missed doses of BCD-057/Humira® (e.g. the patient should not double the next dose of BCD-057/Humira® if he/she have missed the previous one).

During the treatment with adalimumab, the following events have been reported: infections (including tuberculosis and reactivation of hepatitis B), neurological disorders in patients with demyelinating diseases of the CNS, malignancies, allergies, hematological complications (including pancytopenia and aplastic anemia), lupus-like syndrome, and allergic reactions. Adalimumab should be discontinued if the patient develops a serious infection or sepsis, tuberculosis, a severe fungal infection, symptoms suggesting a demyelinating disease, a malignancy, serious allergic reactions, significant blood abnormalities, severe CHF and/or symptoms of lupus-like syndrome.

The investigator decides whether to discontinue the therapy (temporarily or permanently) taking into account the patient's complaints and general health state, physical exam results, laboratory values, and other factors indicating that continuation of the study therapy is not possible, dangerous to the patient or does not benefit the patient's well-being and safety.

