### ***8.2.2. Methods and timeframes for assessment and documenting of safety variables***

The safety population will include all randomized patients (ITT population). In addition, the study report will contain data on serious adverse events reported during screening (if any).

The safety evaluation is based on the frequency and pattern of AEs/SAEs, laboratory abnormalities, and vital sign abnormalities in the therapy arms. Patients will undergo regular physical examination (including blood pressure, pulse, and body temperature checks), CBC and biochemistry tests, urinalysis, ECG, and chest X-ray and/or fluorography.

The frequency of these procedures is shown in Table 12, section 4.6.1 *Study Visits and Procedures*. AEs/SAEs will be documented and reported in accordance with the Sponsor's Manual.

The investigator is responsible for recording adverse events in the clinical study.

AEs must be captured starting from the first dose of the investigational product and through 4 weeks after the last dose. AEs related to the protocol procedures must be recorded from the moment the subject signed the ICF. SAEs must be captured from the moment the patient signed the ICF and through 4 weeks after the last dose of the investigational product. The study investigator can report SAEs that occurred after the required follow-up if he/she considers them related to the investigational product or study procedures.

The study investigator must document non-serious AEs in the source documents and in the CRF, and show them to the CRA at the next monitoring visit. All serious adverse events (SAEs) must be reported to the Sponsor immediately (**within 24 hours**). Reports must be sent to the Sponsor immediately (within 24 hours) by [contact] (ext. 116), addressed to PV Officer, JSC BIOCAD, or by e-mail [[contact]](mailto:[contact]) (with "To PV Officer" in the subject field). The investigator should receive a receipt/delivery confirmation. Information regarding unexpected adverse reactions must be presented to the CRA at the next scheduled visit.

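### The SAE definition has no criterion for other medically important events, so a malignancy or opportunistic infection managed without admission is formally non-serious

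*Protocol*

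**What the plan says.** Section 8.1.1.2 defines seriousness by a closed list. The lead-in is "A Serious Adverse Event (SAE) is any untoward medical occurrence that at any dose". The items are death, threat to life, hospitalization or its prolongation, "Results in persistent or significant incapacitation or disability", and last "Is a congenital anomaly or birth defect". The text then narrows two of them: a threat to life means an immediate risk of death, and hospitalization means official admission.

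Two further provisions in the same section bear on the point:
- A default for doubt: "In case of any uncertainty whether the event meets the seriousness criteria or not, it should be treated as as a serious adverse event".
- A list of items handled like SAEs: "Certain information not considered an SAE must be recorded, presented in the report, and followed up as an SAE". It covers use in pregnancy and breastfeeding, overdose, accidental use, medication errors and death. It names no malignancy, tuberculosis, opportunistic infection or demyelinating disease.

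Section 8.2.2 sends SAEs to the sponsor within 24 hours. Non-serious events go into the source documents and the CRF, and the investigator must "show them to the CRA at the next monitoring visit". Section 8.3.2 requires the SAE Report Form for SAEs only. Under section 12.1, the sponsor reviews SAE reports and may suspend the study, and local ethics committees are told of related SAEs.

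Elsewhere the protocol ranks the risks itself. Section 1.4.2: "The most dangerous adverse effects of adalimumab include serious infections and malignancies". Section 6.1.3.1: "Adalimumab should be discontinued if the patient develops a serious infection or sepsis, tuberculosis, a severe fungal infection", in a list that goes on to symptoms suggesting demyelination and to malignancy. Section 8.1.2 has a safety endpoint that counts these event types by arm.

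**The concern.** The events that the protocol regards as most dangerous can meet none of its seriousness criteria. A skin cancer excised in clinic, or an opportunistic infection treated with oral drugs at home, involves no admission, no immediate risk of death and possibly no disability.

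Three things depend on that classification: whether the event appears among the SAEs, whether the sponsor receives a 24-hour report with the full SAE form, and whether ethics committees are told of a related case. Section 9.5 specifies no statistical stopping criteria, so expedited SAE reporting carries much of the ongoing safety oversight that the protocol describes. The term serious infections, used in sections 6.1.3.1 and 8.1.2, has no definition of its own and may inherit the same gap.

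**Working it through.** **1. Does any provision supply the missing criterion?**

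| Provision | Effect on an outpatient, non-disabling malignancy or opportunistic infection |
|---|---|
| Five criteria, 8.1.1.2 | None met |
| Default for doubt, 8.1.1.2 | Settles doubt about a listed criterion; adds no criterion |
| Items handled like SAEs, 8.1.1.2 | Event types not named |
| Sponsor's Manual, cited in 8.2.2 and 8.3.1 | Cited for documenting and reporting; 8.1.1.2 does not refer to it for seriousness |

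Such an event is non-serious as the text stands.

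**2. What does the event then miss?** The SAE listings, the 24-hour SAE report (8.2.2), the SAE form with narrative and investigations (8.3.2), and the ethics-committee notice of related SAEs (12.1).

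**3. What does it not miss?**
- Sections 4.8.2 and 5.3 require notice to the sponsor within 24 hours, with the reason, of any premature withdrawal. Active tuberculosis is a named withdrawal criterion. So is an adverse event that, in the investigator's opinion, makes participation dangerous.
- Missing two consecutive injections is also a withdrawal criterion. On the two-weekly schedule the second missed injection falls two to four weeks after the drug is stopped. Lasting discontinuation therefore usually leads to withdrawal and its notice, but later than an SAE report would arrive. It cannot do so when fewer than two injections remain.
- The eCRF is due within 5 working days of the visit (4.7.18).
- Section 8.1.2 counts malignancies, tuberculosis, opportunistic infections, demyelinating diseases and lupus-like syndrome by type and arm, whatever their seriousness. Its first endpoint takes AEs and SAEs together, and none of its endpoints is an SAE-only proportion.

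**4. Scale.** The plan gives no figure to reproduce. Inputs: 344 patients (4.2); 55 weeks of observation (1.5.1); 2.4 malignancies per 100 patient-years in psoriasis and 0.22 tuberculosis cases per 100 patient-years across 47 controlled studies (1.4.2). Both arms receive adalimumab, so the rates apply to all patients.

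- Exposure: 344 × 55/52 = 363.8 patient-years, assuming no dropout.
- Malignancies: 363.8 × 0.024 = 8.7.
- Tuberculosis: 363.8 × 0.0022 = 0.8.
- Together: 8.7 + 0.8 = 9.5.

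The share managed without admission is not stated. Over 0 to 100%, between 0 and about 9 events could fall outside the definition. In the M03-656 summary (1.3.2.3), 7 of the 9 malignancies were non-melanoma skin cancers, so a share well above zero is plausible, but the document does not give it.

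**The case against.** The strongest reply is that little is lost. The sponsor learns of tuberculosis, and of any event that ends participation, within 24 hours. The eCRF follows within 5 working days. The event types have their own endpoint. The definition applies equally to both arms of a blinded randomised comparison. The Sponsor's Manual, which is not shown, may hold an expedited list.

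Most of this stands and limits the point. It does not close it. A withdrawal notice is not an SAE form and does not trigger ethics-committee notice. Of the events at issue, only active tuberculosis is named as a withdrawal criterion, and the protocol's own definitions allow discontinuation of drug without withdrawal. Counting by type does not correct the SAE classification. The manual cannot be assessed, and the protocol does not defer to it for the definition.

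A reader might infer more than the documents support:
- *That the sponsor hears of these events only at the next monitoring visit.* The withdrawal and eCRF routes contradict this.
- *That the events disappear from the safety analysis.* Section 8.1.2 counts them.
- *That demyelinating disease is formally non-serious.* Section 8.1.1.2 explains disability broadly enough that such disease may qualify, and doubt resolves towards SAE.
- *That a particular number of events will be misclassified.* Any figure inside the 0 to 9 range would need an outpatient share that the protocol does not give.

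**Conclusion.** The omission is real. The protocol's SAE definition lacks a criterion for other medically important events, and this fits poorly with its own account of the main risks of adalimumab. The effect falls mainly on SAE classification, SAE-form reporting and ethics-committee notice. Timeliness suffers only for events that do not lead to prompt withdrawal. The treatment comparison and the by-type safety endpoint are largely unaffected, except that the meaning of serious infections is left open.

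About 8.7 malignancies and 0.8 tuberculosis cases are expected, of which between 0 and about 9 events in all could be affected. This assumes no dropout and that the quoted rates carry over to this trial. The tuberculosis rate is not specific to psoriasis, and active tuberculosis reaches the sponsor within 24 hours through withdrawal in any case. The point is worth acting on because the change is cheap, not because the present wording hides these events.

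**What to change.** 1. In section 8.1.1.2, add other medically important event as a sixth criterion. Give as examples, to be reported as SAEs, event types already listed in section 8.1.2: malignancy, tuberculosis, opportunistic infection, and demyelinating disease or lupus-like syndrome when no other criterion already covers them.
2. In section 8.1.2, state that serious infections uses the same definition.
3. Reconcile sections 8.1.1.2, 8.1.2 and 8.2.2, so that the events counted as of special interest and the events reported within 24 hours follow one rule. Align the SAE form wording.

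The cost is wording, a few extra 24-hour reports and a slightly higher SAE count in both arms. Sample size, visits and the primary analysis do not change.

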#### **8.1.1.3. Unexpected adverse events**

An unexpected adverse reaction is an adverse reaction, the nature or severity of which is not consistent with the applicable product information (e.g., Investigator's Brochure for an unapproved investigational medicinal product).

#### **8.1.2. Safety endpoints**

- The proportion of patients who developed AEs/SAEs that, in the investigator's opinion, are related to Humira® or BCD-057, by study arms.
- The proportion of patients who experienced grade 3/4 AEs (CTCAE v. 4.03) that, in the investigator's opinion, are related to Humira® or BCD-057.
- The proportion of patients who developed AEs potentially due to TNF $\alpha$  inhibitors, by study arms. Such AEs include infections, serious infections, opportunistic infections (infections caused by opportunistic pathogenic viruses or cellular organisms), tuberculosis, malignancies, demyelinating diseases, lupus-like syndrome, congestive heart failure, allergic reactions, injection site reactions, and CBC or blood biochemistry abnormalities.

- The proportion of patients who discontinued the study due to AEs/SAEs, by study arms.

## ***8.2. Methods and timeframes for assessment, documenting and analysis of safety variables***

### ***8.2.1. Timeframes for analysis of safety variables***

Safety endpoints will be analyzed throughout the entire study.

### ***8.2.2. Methods and timeframes for assessment and documenting of safety variables***

The safety population will include all randomized patients (ITT population). In addition, the study report will contain data on serious adverse events reported during screening (if any).

The safety evaluation is based on the frequency and pattern of AEs/SAEs, laboratory abnormalities, and vital sign abnormalities in the therapy arms. Patients will undergo regular physical examination (including blood pressure, pulse, and body temperature checks), CBC and biochemistry tests, urinalysis, ECG, and chest X-ray and/or fluorography.

The frequency of these procedures is shown in Table 12, section 4.6.1 *Study Visits and Procedures*. AEs/SAEs will be documented and reported in accordance with the Sponsor's Manual.

The investigator is responsible for recording adverse events in the clinical study.

AEs must be captured starting from the first dose of the investigational product and through 4 weeks after the last dose. AEs related to the protocol procedures must be recorded from the moment the subject signed the ICF. SAEs must be captured from the moment the patient signed the ICF and through 4 weeks after the last dose of the investigational product. The study investigator can report SAEs that occurred after the required follow-up if he/she considers them related to the investigational product or study procedures.

The study investigator must document non-serious AEs in the source documents and in the CRF, and show them to the CRA at the next monitoring visit. All serious adverse events (SAEs) must be reported to the Sponsor immediately (**within 24 hours**). Reports must be sent to the Sponsor immediately (within 24 hours) by [contact] (ext. 116), addressed to PV Officer, JSC BIOCAD, or by e-mail [[contact]](mailto:[contact]) (with "To PV Officer" in the subject field). The investigator should receive a receipt/delivery confirmation. Information regarding unexpected adverse reactions must be presented to the CRA at the next scheduled visit.

